## Abstract

**Introduction:**

A cohort of 12 000 children in the Philippines who had enrolled in a 2000–2004 (current ages 16 to 20 years) Phase 3 11-valent pneumococcal conjugate vaccine for the prevention of radiographically confirmed pneumonia are now being asked to participate in a separate study (expected completion date September 2021) to assess the cohort’s current long-term audiometric and otologic status. This new study would allow assessments of the utility of the pneumococcal vaccine in conferring its protective effects on the long-term sequelae of otitis media (OM), if any. Lack of trained local healthcare providers in otolaryngology/audiology and testing equipment in Bohol, Philippines, necessitates the development of a distinct methodology that would lead to meaningful data analysis.

**Methods and analysis:**

Reliable data collection and transfer are achieved by a US otolaryngologist/audiologist team training local nurses on all procedures in a didactic and hands-on process. An assortment of portable otolaryngologic and audiologic equipment suitable for field testing has been acquired, including an operating otoscope (Welch-Allyn), a video-otoscope (JedMed), a tympanometer with distortion product otoacoustic emission measurements (Path Sentiero) and a screening audiometer (HearScreen). Data will then be uploaded to a Research Electronic Data Capture database in the USA.

Tympanometric and audiologic data will be codified through separate conventional algorithms. A team of paediatric otolaryngology advanced practice providers (APPs) have been trained and validated in interpreting video otoscopy. The protocol for classification of diagnostic outcome variables based on video otoscopy and tympanometry has been developed and is being used by APPs to evaluate all otoscopy data.

**Ethics and dissemination:**

The study was approved by the Research Institute of Tropical Medicine, Alabang, Manila, Philippines, and the institutional review board and the Colorado Multiple Institutional Review Board of the University of Colorado School of Medicine, Aurora, Colorado, USA.

Research results will be made available to children and their caregivers with abnormal audiologic outcomes, the funders and other researchers.

**Trial registration number:**

ISRCTN 62323832; Post-results.

Strengths and limitations of this studyThis large-scale study involves data collection in the Philippines and data transfers to the USA; thereby, a completely novel population-based audiometric and otoscopic assessment methodology needs to be developed.This methodology allows for the efficacy evaluation of a randomised controlled trial of pneumococcal vaccine conducted between 2000 and 2004 on the long-term complications of otitis media (OM) (chronic suppurative OM and its sequelae on the hearing).Despite in-depth training of local nurses to collect data and USA’s advanced practice providers to categorise video-otoscopic data, this methodology contains some degree of human factors and subjectivity that may lead to bias.This methodology lacks the ability to resolve inferior quality data or missing data due to logistic and geographic constraints resulting in decreased usable data for analysis.

## Introduction

Otitis media (OM) and its most consequential complication, chronic suppurative OM (CSOM), are disproportionally overrepresented in developing countries, particularly in Asia and Sub-Saharan Africa.^1^ The burden of disease is a spectrum of complications, which include hearing loss, tympanic membrane (TM) perforation, otorrhoea, adhesive OM/retraction pocket, cholesteatoma and intratemporal and intracranial complications, which in turn could have important downstream social, educational and vocational impacts. OM global health initiatives and clinical research in these populations mandate accurate epidemiologic assessments in low-income and middle-income countries (LMICs).

However, large-scale otoscopic and audiometric assessment of ear disease in children in LMIC is difficult due to logistical constraints, including a lack of portable equipment and trained audiologists and otolaryngologists with the time and interest for these studies. A survey^2–8^ of published reports in the past 15 years with relevance to OM through population studies in LMIC has revealed one or more methodologic deficiencies, namely, small sample size, lacking either otoscopic or audiometric evaluation, and particularly, assessment of CSOM.

Two recent studies have overcome these apparent deficiencies, including the documentation of frequencies of CSOM through large-scale population surveys in at-risk regions, including Asia (Indonesia)^9^ and Africa (Kenya).^10^ However, both of these studies relied heavily on onsite local highly trained otolaryngologists and audiologic personnel. In the Indonesian study, locally trained certified audiologists conducted hearing testing while in the Kenyan study; trained specialised medical officers were used to carry out clinical assessments and audiometric assessments. Both studies required significant time commitments of local trained audiologic personnel and senior otolaryngologists to conduct the studies. Both studies were carried out by research teams visiting schools and conducting cross-sectional studies over 3–5 days at each school that lasted for several months. However, while this strategy works for time-limited cross-sectional studies in LMIC, this strategy will not work in long-term longitudinal prospective studies.

## Background

We had to develop a novel methodology to study the impact of an 11-valent pneumococcal conjugate vaccine on long-term audiometric and otologic outcomes of a birth cohort of 12 000, previously enrolled in a randomised clinical trial,^11^ 15–18 years prior. The study is being conducted on Bohol island, Philippines, with limited otolaryngology (two general otolaryngologists on the island) and audiology (one facility with a hearing booth) resources. After piloting hands-on training of local nurses in Bohol, Philippines, to conduct otoscopic and audiologic assessments,^12^ we have refined and standardised all research definitions and protocols outlined in this manuscript.

### Study Site

Bohol, Philippines, is located 640 km south of Manila and its land mass consists of Bohol island and 75 minor surrounding islands (total area of 4 821 km^2^). It has a population of over 1.3 million inhabitants (2015 census) with a population density of 270/km^2^. The local economy is sustained by tourism and agriculture. The 2018 poverty rate (defined as a family of five earning less than PhP 7337 a month (equivalent to US$144)) in Bohol was reported to be 21.1% (http://www.psa.gov.ph/poverty-press-releases/nid/138411).

### Subjects of the study

The study cohort consists of a potential of over 12 000 Filipino children who were enrolled in a pneumococcal vaccine trial conducted in Bohol 2000 to 2004 between the ages of 6 weeks and 10 weeks. For the current study, these same subjects will be approximately between 16 years and 20 years of age.

### Study Aim

The specific aim of the methodology is to obtain otoscopic and audiologic data from enrolled subjects to enable assignment of OM-related and audiometric diagnostic outcomes to each of the study subjects. To achieve this goal, the methodology has the following key components: (1) portable testing equipment, (2) training of local research personal using the testing equipment, (3) development of a protocol for data collection, storage and transfer, (4) cataloguing tympanometric data using published metrics, (5) video-otoscopy data and diagnosis outcome classifications and (6) training USA’s advanced practice providers (APPs) in video otoscopy. A detailed description of each of the steps is further elucidated below.

### Testing equipment

Each testing device was chosen for its portability, technical capabilities and potential reliable performance in the tropics, particularly, being able to be transported for field use.

An otoscope with an operating head (21700, Welch-Allyn, Skaneateles Falls, New York, USA) was selected to initially obtain a sufficient view of the TM for subsequent video otoscopy. Associated micro-instruments were selected to clear cerumen if the tympanic membrane (TM) could not be adequately visualised.A portable, rechargeable battery-operated video otoscope able to capture and record high-definition (1080 p) still images and streaming video was chosen (Horus+HD Video Otoscope, JedMed, St Louis, Missouri, USA). Images are initially recorded on SD cards in the field and subsequently transferred to hard discs at the research office.A portable, rechargeable battery-operated tympanometry and distortion product otoacoustic emission (DPOAE) device (Path Sentiero, model SOD07, Path Medical, Germering, Germany) was selected. While the device has many functionalities, only a limited number were required for the study. The 226 Hz frequency tympanogram issued at a pressure range of −600 daPa to +400 daPa. The tympanometer outputs for each ear include a tracing viewable by the tester as well as physical measurements of ear canal volume (ml), peak pressure (daPa), peak compliance (ml) and tympanic width (daPa). DPOAE is used as a screening tool and measured at 2 kHz, 3 kHz and 4 kHz for each ear. Although detailed results are available through the device, only the basic results with outputs as ‘pass’ or ‘refer’ are to be used since DPOAE is only being used as a screening tool for hearing loss.A portable, rechargeable battery-operated screening audiometry system (HearScreen, HearX, Pretoria, South Africa) has been chosen coupled with a smartphone (Samsung Galaxy 12) and an ISO calibrated noise-cancelling headphone (Sennheiser HD280-pro Circumural Headphone (0.5–8 kHz)). The device uses an automated testing protocol to test pure tone frequencies at 0.5 kHz, 1 kHz, 2 kHz, 3 kHz, 4 kHz, 6 kHz and 8 kHz for each ear at sound intensity levels of 20–70 dB HL. The device then generates a pass or fail interpretation based on published best practice guidelines. Subjects that fail the screening audiogram are referred for a diagnostic audiogram at Bohol Hearing Centre. All HearX data are stored on remote servers and can be accessed by the research team.

### Training of local research personnel

The training of local Filipino nurses by a US otolaryngology/audiologist team has been described previously.^12^ Briefly, four nurses were trained didactically on the topic of OM and the basics of audiology and its relationship to OM clinically. Then they were given hands-on training in otoscopy, cerumen removal, video otoscopy and all of the audiologic equipment to perform tympanometry, DPOAE and screening audiograms. The training session culminated in the nursing team obtaining video-otoscopic, audiologic and clinical data from 47 subjects under direct supervision of the US otolaryngologist/audiologist team.

### Protocols for data collection, storage and transfer protocols

Research data collection by the local research team include: (1) case report forms; (2) video-otoscopy and audiologic testing and 3) miscellaneous data.

#### Case report form (CRF)

Each research subject has an original paper CRF, which contains patient identifiers and clinical information entered by the research personnel following a parental interview with ear-specific medical history (ie, ear infection, discharge, TM perforation and hearing loss). CRFs collected during the week are uploaded by the research nurse into a Research Electronic Data Capture (REDCap) database hosted at the University of Colorado Denver School of Medicine, Aurora, Colorado, USA.

#### Video-otoscopy and audiologic testing

Subjects whose TMs are devoid of cerumen or whose cerumen can be cleaned by the research nurses undergo video-otoscopy and audiologic testing. All subjects whose cerumen cannot be cleaned adequately are given a bottle of mineral oil and a medicine dropper and advised to use 5 drops twice a day for 7 days and asked to return for another assessment. However, subjects that fail to have adequate cerumen removal after the subsequent visit or had active otorrhoea are referred to the local otolaryngologist for further management

The research nurses record the two ears of a research subject in a regimented sequence for ease of review by the APPs at a subsequent time (right ear still photo, left ear still photo, right ear video and left ear video). SD cards are downloaded at the end of each weekday and images stored on two hard disks (original and backup disks). Data are transferred to the USA by external drives.

Audiologic testing data are processed in the following manner. The four discreet outputs produced by the tympanometer are used to determine tympanogram types. An overlay ‘rectangle’ onto the tympanometer tracing is used by the manufacturer to include most ‘normal’ tympanograms within these confines as defined by Jerger^13^ to assist with diagnosis. The local research team uses this real-time judgement call for a ‘pass’ or ‘fail’ depending if the peak of the tracing is within the ‘normal’ ranges as dictated by the ‘rectangle’. DPOAE results are also automatically determined by the device as either ‘pass’ or ‘refer’. Hearing screening done on subjects using the HearScreen device also classifies subjects as ‘pass’ or ‘fail’ by the device. All subjects who fail the tympanogram, DPOAE or HearScreen are referred to Bohol Hearing Centre for diagnostic audiometry. All raw tympanogram, automated DPOAE, automated HearScreen and raw HearX data are entered by the research supervisor to the REDCap database on a weekly basis.

#### Miscellaneous data

All audiologic data from Bohol Hearing Centre, as well as all otologic diagnoses made by the island otolaryngologist, are also entered into the REDCap database by the research supervisor on an as-needed basis.

### Cataloguing of tympanometric data

The tympanometric data for each ear consisting of ear canal volume (ml), peak pressure (daPa), peak compliance (ml) and tympanic width (daPa) are sorted based on the classic classification established by Jerger: A, B, C, A_s_ and A_d_ types. As such, a portion of data would result in tympanometric parameters landing outside of the confines for each type defined by Jerger.^13^ Since the research team viewed it imperative that each video otoscopy be accompanied by a tympanogram type to aid in video-otoscopy interpretation, an ad hoc methodology had to be developed to capture the ‘non-classifiable’ tympanograms. The study otolaryngologist and a senior audiologist independently will read all ‘non-classifiable’ tympanograms, and discordant classifications will be adjudicated by a second senior audiologist. The majority vote will confirm the classification type.

### Video-otoscopy data and diagnosis outcome classifications

Video-otoscopy analysis leading to disease classification takes into account all otoscopic abnormalities associated with acute OM, chronic non-suppurative OM and CSOM, as well as a non-OM diagnoses (eg, otitis externa) summarised in box 1. APPs document findings rather than immediately arrive at a diagnosis. Each video-otoscopic image is associated with a tympanogram type as to simulate pneumatic otoscopy, a proxy for the gold standard to diagnose middle-ear effusion.^14 15^ The gold standard for the presence of middle-ear fluid is detected only by myringotomy; however, this being impossible, the proxy methodology used here is based on the decisions made by the senior paediatric otolaryngologist with over 30 years of performing otologic procedures for complications from OM, including tympanoplasties and mastoidectomies. Given it would be impractical and impossible for the paediatric otolaryngologist to view thousands of video otoscopies, experienced otoscopists (APPs) have been trained and validated in identifying otoscopic abnormalities listed in box 1.

Box 1List of video-otoscopic finds depicting physical findings associated with otitis mediaRedness of tympanic membrane (TM).Opacification not due to scarring (dullness, thickened and webbing).Bubbles or air-fluid interfaces or fluid.Abnormal TM colour: white, yellow, amber or blue.Fullness or bulging of TM.Thinned out area of TM or healed perforation seen in 360°.Tympanosclerosis/scarring.Perforation small (<25% of TM).Perforation large (≥25% of TM).Retraction/retraction pocket/generally thinned out but not healed TM.Retraction/pocket bottom not seen.Otorrhoea not due to otitis externa (moisture).Granulation tissue or squamous debris.Otitis externa.

All video otoscopies that are deemed as poor quality by the APP are reviewed by the otolaryngologist of the study and would remained classified as poor quality or into one or more of the following TM findings.

Video-otoscopic findings for each ear will then merged with the four tympanometric output parameters and clinical medical history to arrive at discreet diagnoses (figure 1). Four broad diagnostic categories with definitions include normal, mild, moderate and severe ear disease. If two ears of a subject have disparate levels of middle-ear disease, the subject would be classified as having the more serious form of ear disease for the purpose of analysis.

**Figure 1 F1:**
[figure not shown]
Schema in classifying tympanometric types based on tympanometer outputs (accordance with Jerger classification). ECV, external canal volume; ENT, Ear, Nose, and Throat physician, or Otolaryngologist.

#### Normal

No evidence of ear disease as determined by no disease-related video-otoscopic findings regardless of tympanometric abnormal states and clinical medical history of ear disease.

#### Mild Ear Disease

Acute OM: the presence of at least two of the following three otoscopic signs: (1) white, yellow, amber or blue TM (ie, abnormal colour), (2) opacification not due to scarring, (3) tympanometry peak compliance <0.2 mL or tympanometric width >200 daPa on tympanometry, or bubbles or air-fluid interfaces, and one of the following three signs/symptoms: (a) ear pain, (b) redness of the TM and (c) fullness or bulging of the TM or acute purulent otorrhoea not due to otitis externa.^16–18^OM with effusion (OME): the presence of at least two of the following three otoscopic signs: (1) white, yellow, amber or blue TM (ie, abnormal colour), (2) opacification not due to scarring, (3) tympanometry peak compliance <0.2 mL or tympanometric width >200 daPa from tympanogram, or bubbles or air-fluid interfaces, and the absence of the following four signs/symptoms: (a) ear pain, (b) redness of the TM, (c) fullness or bulging of the TM or (d) acute purulent otorrhoea not due to otitis externa.^16–18^Healed perforation: otherwise normal TM with a thinned-out area of TM.Myringosclerosis: a hardening of the ear drum as calcium deposits form on the ear drum and middle ear, peak compliance on tympanogram >5.0 mL.

#### Moderate ear disease

Dry perforation: perforation of the TM without otorrhoea or ear canal volume ≥2 mL on tympanogram.Adhesive OM: intact TM but retraction or retraction pocket seen.

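### Read naturally, the Dry perforation definition lets ear canal volume alone make an ear Moderate, while the Normal definition disregards tympanometry, and the text does not say which yields

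*Protocol article*

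**What the plan says.** Four places in the protocol article bear on this.

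- Moderate ear disease: Dry perforation is "perforation of the TM without otorrhoea or ear canal volume ≥2 mL on tympanogram".
- Normal: an ear qualifies when there are "no disease-related video-otoscopic findings regardless of tympanometric abnormal states and clinical medical history of ear disease".
- Video-otoscopy data and diagnosis outcome classifications: "Video-otoscopic findings for each ear will then merged with the four tympanometric output parameters and clinical medical history to arrive at discreet diagnoses". The one severity rule in that section is "If two ears of a subject have disparate levels of middle-ear disease, the subject would be classified as having the more serious form".
- Protocol to deal with ears with incomplete data set: an ear with only a tympanogram, and no otorrhoea or ear pain on the case report form, becomes normal or OME according to tympanogram type. An ear without a tympanogram is classified from the video alone.

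Ear canal volume is one of the four tympanometer outputs (Testing equipment; Cataloguing of tympanometric data). It is not among the otoscopic findings in Box 1, where perforation is recorded by its size on the drum.

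**The concern.** Two stated outcome definitions both fit an ear with a clean, readable video and a volume of 2 mL or more, and they lie two severity levels apart. The merging sentence does not rank video against tympanometry. The severity rule works between a subject's two ears, not between two diagnoses for one ear. Two analysts following the text could code the same ear differently.

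Ear disease classification is the outcome compared between vaccine and placebo, and the Statistical analysis methodology section makes a significant difference the condition for deriving the vaccine-efficacy model. If large volume in an intact ear is unrelated to vaccination, Moderate labels given on volume alone add the same background to both arms. That weakens the comparison and makes the efficacy step less likely to be reached. The more-serious-ear rule raises the share of subjects affected above the share of ears.

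**Working it through.** **Logic.** Let F = any disease-related video finding, P = perforation seen, O = otorrhoea, V = canal volume of 2 mL or more. Then Normal = not F, and Dry perforation, on the natural reading, = (P and not O) or V.

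| Video | Volume | Normal? | Dry perforation? |
|---|---|---|---|
| No finding | below 2 mL | yes | no |
| No finding | 2 mL or more | yes | yes |
| Perforation, no otorrhoea | either | no | yes |
| Perforation with otorrhoea | 2 mL or more | no | yes, although not dry |

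The overlap with Normal is exactly the second row.

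**The other parse.** Dry perforation = P and not (O or V). This removes the overlap, but a dry perforation with a large volume then fails the definition, and no other Moderate or Severe entry takes it. The Mild section favours the first parse: there, tympanometric thresholds are positive criteria joined by *or*. In acute OM and OME, however, tympanometry can supply only one of the two signs required, so it never makes the diagnosis alone. Dry perforation is the only Moderate or Severe diagnosis that a tympanometric number can trigger by itself.

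**Incomplete data.** A large-volume ear with only a tympanogram is normal or OME, never Dry perforation. The same ear with a clean video but no tympanogram is Normal. With both, it is Normal or Moderate, depending on which definition is applied.

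**Size, by assumption only.** The article gives none of these inputs:

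- e, the share of intact ears with V: 1%, 2% or 5%
- t, true moderate-or-severe disease on placebo: 3%
- true VE: 50%, so true disease on vaccine is 0.03 × 0.5 = 0.015
- VE taken as 1 minus the risk ratio, with a moderate-or-severe endpoint

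Let s be the share of subjects without true disease who are labelled Moderate on volume alone. With independent ears s = 1 − (1 − e)². With fully correlated ears s = e.

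Placebo risk = t + (1 − t)s. Vaccine risk = 0.015 + 0.985s. Observed VE = 1 − vaccine risk / placebo risk.

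| Case | e | s | Placebo | Vaccine | Observed VE |
|---|---|---|---|---|---|
| Normal prevails | any | 0 | 0.03000 | 0.01500 | 50% |
| Fully correlated | 1% | 0.0100 | 0.03970 | 0.02485 | 37% |
| Fully correlated | 2% | 0.0200 | 0.04940 | 0.03470 | 30% |
| Fully correlated | 5% | 0.0500 | 0.07850 | 0.06425 | 18% |
| Independent | 1% | 0.0199 | 0.04930 | 0.03460 | 30% |
| Independent | 2% | 0.0396 | 0.06841 | 0.05401 | 21% |
| Independent | 5% | 0.0975 | 0.12458 | 0.11104 | 11% |

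**The case against.** The strongest reply is that the Normal definition is itself the precedence rule. Its clause about disregarding tympanometric abnormality can be read as an override: a clean video makes the ear Normal whatever the canal volume. The article also says that tympanogram type is there to help interpret the video, which is a supporting role. The entry is headed Dry perforation, so volume may have been meant only as corroboration of a hole in the drum. On this reading no ear is misclassified. The reading is reasonable, and it is why zero dilution belongs in the range. It does not settle the matter, because the Dry perforation entry is worded as a second route and nothing says that it gives way.

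A second reply is that the article is condensed. Figure 1 is cited for the diagnoses but not shown, and its abbreviations indicate that canal volume and an otolaryngologist enter the schema somehow. The Discussion mentions a diagnostic algorithm. An ordering may exist in fuller documents. But the figure's caption describes only the typing of tympanograms, so a precedence rule cannot be assumed from it. The point here is a conflict between two definitions the article does state, not a missing detail.

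A third reply is that the size rests on no documented input. That stands in full. The article gives no frequency of large volume in intact ears at 16 to 20 years, and does not name moderate-or-severe disease as the endpoint. Independence of a subject's two ears is also the adverse end of the range if the ears are positively correlated, which is plausible for a size measurement.

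**Conclusion.** Wrong as written; it should be fixed. Read naturally, the two definitions overlap for an ear with a clean video and a volume of 2 mL or more. The visible text does not say explicitly which one yields, and the incomplete-data rules fit neither definition cleanly.

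A reader might infer that the plan will certainly class intact ears as Moderate and lose most of the vaccine effect. The documents do not support that. The Normal definition may override, in which case observed efficacy stays at the true value. The lower figures are illustrations that depend on the assumed 1% to 5% of ears, 3% disease, 50% efficacy, a moderate-or-severe endpoint and large volume being unrelated to arm. What can be said is the direction: if the Dry perforation wording is applied literally, the comparison moves towards the null by an unknown amount. The overlap itself depends on none of these numbers.

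**What to change.** Reconcile the Normal, Moderate ear disease and incomplete-data sections:

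1. Reword Dry perforation so that it cannot be parsed two ways.
2. State a within-ear precedence rule for outcome coding, consistent with the Normal definition: when the video is readable, the otoscopic finding decides the category and canal volume is supporting evidence only.
3. Say how canal volume is used when the video is missing or unreadable, so that the tympanogram-only rule and the Dry perforation entry agree.

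This concerns outcome coding, not care of subjects. It costs a few lines in the algorithm and, if ears have already been coded, a rerun on stored data; no new data are needed. Having the study otolaryngologist re-review stored videos of ears flagged by volume is optional, and its cost depends on a number of ears that the article does not give.
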